### Clinic recruitment

Recruitment will focus on primary care clinics that are part of the DFMCH (n = 20). Clinics offering resident training will be excluded (n = 6); one clinic will be excluded from consideration because one of the systems consultants has an active clinical practice there. We selected the remaining 13 clinics as a recruitment pool to enable systematic monitoring of opioid prescribing rates and other clinical data through the clinical data warehouse housed by the DFMCH. The 13 clinics were first grouped into two categories (community vs. regional) and then ranked by the number of patients with long-term opioid prescriptions (defined as 10+ orders in the previous 12 months). Within these two categories, the clinics were paired by “nearest-neighbour” matching based on number of patients with 10+ opioid prescriptions. One pair of clinics will be recruited from the regional group (2/4 clinics eligible) and three pairs will be recruited from the community group (6/9 clinics eligible). Within each pairing, one clinic will be invited to be the intervention clinic by random selection. If that clinic agrees to participate (via a discussion between the systems consultant and the clinic’s medical director), the second clinic in the pairing will be assigned to the control condition. If the first clinic declines to participate, the second clinic in the pair will be invited to be the intervention clinic. If the second clinic agrees to participate, it will be assigned to be the intervention clinic and the first clinic will be assigned to control. If both clinics decline to participate, an alternate clinic will be selected within each category (there are three alternates among the community clinics and two alternate clinics in the regional clinics) until one of the alternate clinics agrees to participate.

Specific Aim 3 uses mixed methods to understand how the strategy worked, including assessments of feasibility and acceptability (costs, ease of recruitment, fidelity to the protocol, physician acceptance) and preliminary effectiveness (degree of checklist implementation, effect of the strategy on variation in opioid prescribing rates and dosing levels). While multiple prescribers (primary care physicians, nurse practitioners, physician assistants) potentially practice within each clinic, the clinic will serve as the primary unit of analysis. Relevant comparisons for study measures will be made in two ways. First, historical data are available for many study measures, permitting time-series analysis of repeated measures to detect changes in a clinic over time (pre-intervention vs. post-intervention). Second, we can compare intervention and control clinics per the matched-pairs design.

### Measures

This proposal uses the RE-AIM model as an organizing evaluation framework [48] to examine the quality, speed and impact of implementing the SCS in primary care settings. RE-AIM assesses implementation in five dimensions: Reach, Effectiveness, Adoption, Implementation, and Maintenance. This evaluation seeks to meet the standards for ‘fully developed use’ of RE-AIM [49] by employing the RE-AIM checklist available at www.re-aim.org. We have, however, chosen to omit one RE-AIM dimension (maintenance at the setting level) because assessing this dimension would require follow-up 6 months after project funding ends. Specific measures for each RE-AIM dimension are presented in Table 1.

**Table 1 Tab1:** RE-AIM measures

Domain	Measure
Reach	Number and percentage of patients excluded
Reach	Number and percentage of patients served by eligible clinics
Reach	Characteristics of participating patients versus general patient population
Reach	Structured interview with Family Medicine director to qualitatively assess recruitment process
Effectiveness	Number and percentage of patients completing urine drug screens
Effectiveness	Overall rate of opioid prescribing by clinic and provider
Effectiveness	Number and percentage of patients screened for mental health/substance use problems
Effectiveness	Overall rate of opioid/benzodiazepine co-prescribing
Effectiveness	Number and percentage of patients signing pain agreements
Effectiveness	Number and percentage of opioid prescriptions above 120 mg daily morphine equivalent
Effectiveness	Number and percentage of providers who drop out of study at 3 months
Effectiveness	Structured interview with clinic lead to assess satisfaction, effectiveness, and subgroup differences
Adoption (Setting)	Number and percentage of clinics excluded
Adoption (Setting)	Number and percentage of clinics that participate
Adoption (Setting)	Characteristics of participating clinics versus non-participants
Adoption (Staff)	Number and percentage of staff excluded
Adoption (Staff)	Number and percentage of staff who participate
Adoption (Staff)	Characteristics of participating staff versus non-participants
Implementation	Hours of consulting delivered/received per provider
Implementation	Adaptations made to consulting protocol during intervention period
Implementation	Cost of consulting intervention
Implementation	Structured interview with clinic lead to assess consistency of consulting intervention
Maintenance (Indiv.)	Number and percentage of patients completing urine drug screens (6-month follow-up)
Maintenance (Indiv.)	Overall rate of opioid prescribing by clinic and provider (6-month follow-up)
Maintenance (Indiv.)	Number and percentage of patients screened for mental health/substance use problems (6-month follow-up)
Maintenance (Indiv.)	Overall rate of opioid/benzodiazepine co-prescribing (6-month follow-up)
Maintenance (Indiv.)	Number and percentage of patients signing pain agreements (6-month follow-up)
Maintenance (Indiv.)	Number and percentage of opioid prescriptions above 120 mg daily morphine equivalent (6-month follow-up)
Maintenance (Indiv.)	Number and percentage of providers who drop out of study (6-month follow-up)
Maintenance (Indiv.)	Focus group with clinicians who made substantial changes

Source*:* Re-aim.org; Measuring the Use of the RE-AIM Model Dimension Items Checklist.

### Quantitative data collection and analysis

We will access many of our RE-AIM measures by tapping into clinics’ electronic health records via a data warehouse maintained in the DFMCH (e.g. reach data such as number and percentage of patients excluded, effectiveness and maintenance data such as overall rate of opioid prescribing by provider, etc.). The representativeness of the sample (patients, clinics, and staff) will be accessed through administrative databases maintained by the DFMCH. The quantitative analysis will focus primarily on patient-level opioid prescription rates measured in MEDD. Changes in outcomes will be assessed through repeated monthly observations. Data on prescribing will be augmented by other process and outcome measures shown in Table 1.

### Statistical model

To isolate and measure the intervention effect on each measure of interest, we will fit a mixed-effects model to the data. The model will contain a fixed effect for a shared common linear trend; we will test the sensitivity of the results to other non-linear trends. Fixed effects will be included for the impact of the intervention on the measure of interest. Since the intervention activities will be skewed toward the beginning of the intervention period, we will model an increasing cumulative effect that allows the rate of increase to change during the period. That is, we will use a piecewise linear function of the intervention duration with ‘knots’ at the start and midway through the 12-month period. At the end of the intervention period, we will allow for a second linear progression to capture any continuing effect or any regression back to pre-intervention response levels. Other fixed effects will be included for observed characteristics of providers that may have a significant impact on the response variable (e.g. patient/physician ratio). Random effects will be included to allow for correlation among repeated observations within the same clinic, provider, or patient. Auto-correlated model error terms will be included to allow for additional correlation among observations from the same patient in adjacent months. Appropriate transformations of the response variable (e.g. logarithms, square roots, etc.) will be considered to avoid negative fitted values and to better match the frequency of outlying values.

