Specific Aim 2 focuses on field-testing the SCS implementation strategy. The systems consultants’ approach to interacting with clinics is modelled after the coaching protocol used in NIATx 200, which included in-person site visits and regular follow-up through phone and email communication. Participating clinics will be paired with a systems consultant to work through the SCS over a 6-month period. Each clinic will designate one clinician to act as a clinic leader in working with the systems consultant. The clinic leader will host two site visits by the systems consultant and communicate with the consultant monthly during the 6-month follow-up consulting period via phone and email. The clinic leader will work with a clinic’s “change team”—a group of 2 to 6 other staff members involved in opioid prescribing to identify and implement systems changes to improve opioid prescribing processes. The consultant’s initial site visit will last about 2 hours. The consultant will start by presenting the latest research on balancing the benefits and risks of long-term opioid use. The visit will include reviewing information gathered by the change leader before the site visit as a result of conducting a walk-through exercise, in which the change leader follows the clinic process for refilling an opioid prescription for a current patient, step-by-step. The visit will also help the change team determine the best course for implementing aspects of the checklist, depending on the clinic’s own workflow. The systems consultant will help synthesize baseline information from the walk-through and other activities and facilitate a brainstorming session with the change team using nominal group technique [28]. The systems consultant and change team will envision how to implement the checklist, assessing any systemic barriers to implementation. The systems consultant and clinic leader will debrief to develop an implementation plan and schedule a second site visit to assess progress. Throughout the intervention period, the systems consultant will help the team implement ideas for change using Plan-Do-Study-Act change cycles [29] and maintain monthly email and phone contact with the clinic leader and change team to monitor implementation progress and offer advice. The systems consultant will also be available to discuss patient care issues (e.g. difficult cases) during monthly phone conferences, with all identifiable patient data removed beforehand.

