### Milestones and products of pilot test

The primary goal of this project is to obtain pilot data for a large-scale clinical trial of different approaches to EBP adoption in healthcare. The research will be critical in developing (1) specifics of the guideline to be implemented, and (2) supports provided via the SCS implementation strategy and the systems consultants who deliver it. The protocol will be determined to be feasible if we enroll four intervention clinics, deliver the intended intervention in all four clinics, follow the clinics for a 6-month period, and obtain quantitative and qualitative data from participating clinicians. Acceptability will be gauged by assessing fidelity to the protocol and analysing qualitative data collected by the research team. We will continue to track effectiveness measures through the end of the 3-year grant period using de-identified electronic health records (e.g. opioid prescribing rate by clinician, number of treatment agreements signed) to assess the preliminary effectiveness of the SCS on clinical practice. With eight clinics reporting data (four intervention and four control clinics), we will be able to obtain baseline estimates of means and standard deviations for RE-AIM outcomes and point estimates of treatment effect sizes, thereby equipping us to conduct an accurate power calculation for the follow-up randomized trial.

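### The effect model places its knots on a 12-month period although consulting lasts 6 months, so no knot falls inside consulting and months 7–12 are labelled as intervention

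*Protocol article*

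**What the plan says.** The Specific Aim 2 paragraph (printed under Preliminary studies) sets the length of the intervention: "Participating clinics will be paired with a systems consultant to work through the SCS over a 6-month period". It adds that the clinic leader will "communicate with the consultant monthly during the 6-month follow-up consulting period via phone and email". Milestones and products of pilot test makes it a condition of feasibility to "follow the clinics for a 6-month period".

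The Statistical model section gives its reason for a change of slope: "Since the intervention activities will be skewed toward the beginning of the intervention period", the effect should be able to build up at a changing rate. It then makes the effect piecewise linear in intervention duration, with knots "at the start and midway through the 12-month period". After that: "At the end of the intervention period, we will allow for a second linear progression to capture any continuing effect", or a return towards earlier levels.

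Table 1 (Measures) lists maintenance rows such as "Number and percentage of patients completing urine drug screens (6-month follow-up)", without saying whether the 6 months run from the start or the end of consulting.

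**The concern.** The model is written as a function of intervention duration, but the only duration it names is 12 months, and the intervention described elsewhere lasts 6. Placed by the 12-month figure, the mid-period knot falls in the month when consulting ends. Two things follow on the plain reading.

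- The whole of consulting is one straight line, so the model cannot show the early build-up that the section gives as its reason for having the knot.
- The six months after consulting carry the label of intervention, and the segment meant to show persistence or regression starts six months after support has stopped.

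At stake is what the reported coefficients mean. The pilot is to supply point estimates of effect size for the power calculation of the later trial (Milestones). An effect quoted for the end of the intervention period could refer to month 6 or month 12, depending on which section the analyst follows.

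**Working it through.** **Step 1: the stated lengths side by side.**

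| Place | Length | What it refers to |
|---|---|---|
| Specific Aim 2 | 6 months | Consulting: two site visits plus monthly contact |
| Milestones | 6 months | Following the clinics, as a feasibility criterion |
| Statistical model | 12 months | Period used to place the knots |
| Table 1, Maintenance | 6-month follow-up | No anchor stated |

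The 12-month figure cannot be reproduced from any other section.

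**Step 2: where the knots fall.** The rule is: start, midpoint, end of the period of length L.

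- L = 12: months 0, 12/2 = 6, and 12. The knot at 12 is inferred from the segment that starts when the intervention ends.
- L = 6: months 0, 6/2 = 3, and 6.
- If 12 months means 6 of consulting plus 6 of follow-up, the knots are at 0 and 6, and the end of intervention coincides with the knot at 6.

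Whenever consulting lasts 6 months and the 12-month figure sets the knots, no knot lies strictly between months 0 and 6.

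**Step 3: what one slope over months 0–6 implies.** The effect is a straight line from zero, so fitted effect at month 3 = ½ × fitted effect at month 6, whatever the data show.

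**Step 4: size, in an assumed example.** The documents give no effect curve, so this one is assumed: −15% at month 3, −20% at month 6, then waning to zero over 6 or 12 months. The fit is noise-free least squares with 8 clinics (4 per arm), 24 months before and 18 after the start, clinic intercepts, a common linear trend and independent errors. Effect at month t = Σ bₖ · max(t − k, 0) over knots k, in intervention clinics only. Entries are percentages.

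| Waning | Knots | Month 3 | Month 6 | Month 12 |
|---|---|---|---|---|
| 6 months | Truth | −15 | −20 | 0 |
| | 0/6/12 | −10.8 | −21.5 | +0.9 |
| | 0/3/6 | −15.9 | −15.9 | −5.6 |
| 12 months | Truth | −15 | −20 | −10 |
| | 0/6/12 | −10.8 | −21.5 | −9.1 |
| | 0/3/6 | −15 | −20 | −10 |

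Check of step 3: 21.5/2 ≈ 10.8. The month-3 effect is understated by (15 − 10.8)/15 = 28%, and the month-6 effect overstated by (21.5 − 20)/20 ≈ 8%. With error autocorrelation of 0.5, knots 0/6/12 give −10.6 at month 3 and −21.2 at month 6.

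Knots 0/3/6/12 return the truth in both rows. This is by construction, since the assumed curves bend only at those months within the 18 months fitted.

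**Step 5: range over other assumed shapes.** Knots 0/6/12, fitted to the intervention-minus-control effect with 12 months before and 18 after the start; effect −10 units at month 6, then a plateau.

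| Build-up | True month 3 | Fitted month 3 | Fitted month 6 |
|---|---|---|---|
| Even | −5 | −5.00 | −10.00 |
| Mildly front-loaded | −6 | −5.20 | −10.39 |
| Strongly front-loaded | −9 | −5.79 | −11.58 |

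With an even build and plateau, knots 0/6/12 and 0/3/6 give identical results.

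**The case against.** The strongest reply is that the harm is limited. Outcomes are observed monthly (Quantitative data collection and analysis) and tracked to the end of the 3-year grant (Milestones), so a reader who infers that outcomes are measured at the wrong time goes further than the documents allow. This stands.

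A reader might also set the model's month-12 value (about 0% or −9%) against the true −20% at month 6 and conclude that the effect is lost. That compares different months. At month 12 the assumed truth is 0% or −10%, and the fitted values are close to it. Because a knot remains at month 6, build-up and later change are still separated. The section also names no month at which the effect is to be read.

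Moving the knots to 0/3/6 is not better in every case. With 6-month waning it gives −15.9% at month 6 against a true −20%, and −5.6% at month 12 against 0, because everything after consulting is forced onto one line. This stands too, and it shapes the fix.

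A reader might infer that maintenance is mistimed. Table 1 does not support that: its 6-month label has no anchor and is not derived from the model's knots. It could mean month 6, 12 or 18, and is an ambiguity to close.

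Finally, 12 months may mean 6 of consulting plus 6 of follow-up. The text does not say so, and on that reading the stated aim of letting the rate of build-up change during the intervention still has no knot to serve it.

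The feasibility criteria do not use this model, and the effect estimates are preliminary. That limits the consequences but does not remove the contradiction.

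**Conclusion.** The point holds in a limited form. The intervention length in the Statistical model section contradicts the 6 months in Specific Aim 2, and the effect model depends on it. If 6 months is right, two things are lost: the knot inside consulting that would show front-loading, and the correct label for months 7–12.

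In the assumed examples the month-3 effect is understated by 28% in step 4. In step 5 the shortfall runs from none (even build) through 13% (5.20 against 6) to 36% (5.79 against 9). The month-6 effect is recovered to within about 8% in step 4 and between 0% and 16% in step 5. All these sizes rest on assumed effect curves and noise-free fits; the documents give neither effect sizes nor variances. They also do not show which length is right. If 12 months is meant, the model is coherent and the other sections need correcting.

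**What to change.** 1. Reconcile Specific Aim 2, Statistical model and Milestones to one stated intervention length.
2. Place knots at the start, midpoint and end of each clinic's actual intervention period, with dates from the consultants' contact logs described under Cost analysis. Start the post-intervention segment at that end.
3. If 6 months stands, this means knots at months 0, 3 and 6. Keep one further knot, for example at month 12, so that change after consulting is not forced onto a single line.
4. State the month at which the intervention effect is read.
5. As a clarification, anchor the 6-month follow-up in Table 1 to the end of consulting.

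The cost is wording, plus one more parameter than the plan as written if the later knot is kept. With eight clinics that costs a little precision. No further data are needed, since monthly records run to the end of the grant. The change should be made before analysis.

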**Methods/Design:**

The pilot test will compare four intervention clinics to four control clinics in a matched-pairs design. A leading clinical guideline for opioid prescribing has been translated into a checklist-based implementation guide in a systematic process that involved experts who wrote the guideline in consultation with implementation experts and primary care physicians. Two physicians with expertise in family and addiction medicine are serving as the systems consultants. Each systems consultant will guide two intervention clinics, using two site visits and follow-up communication by phone and email, to implement the translated guideline. Mixed methods will be used to test the feasibility, acceptability, and preliminary effectiveness of the implementation strategy in an evaluation that meets standards for ‘fully developed use’ of the RE-AIM framework (Reach, Effectiveness, Adoption, Implementation, Maintenance). The clinic will be the primary unit of analysis.

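### The effect model names no clinic-specific time term, so the standard error of an effect delivered to four clinics can shrink with patient numbers rather than clinic numbers

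*Protocol article*

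**What the plan says.** The design is clustered: "The pilot test will compare four intervention clinics to four control clinics in a matched-pairs design". Assignment is at clinic level: "Within each pairing, one clinic will be invited to be the intervention clinic by random selection". The Specific Aim 3 paragraph declares that "the clinic will serve as the primary unit of analysis", and the abstract and the section on potential problems repeat this.

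The data to be analysed lie below the clinic: "The quantitative analysis will focus primarily on patient-level opioid prescription rates measured in MEDD". They are longitudinal: "Changes in outcomes will be assessed through repeated monthly observations".

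The Statistical model section then gives three parts of the structure over time:

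- Trend: "The model will contain a fixed effect for a shared common linear trend; we will test the sensitivity of the results to other non-linear trends".
- Random effects: "Random effects will be included to allow for correlation among repeated observations within the same clinic, provider, or patient".
- Serial correlation: "Auto-correlated model error terms will be included to allow for additional correlation among observations from the same patient in adjacent months".

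The intervention effect is a piecewise linear function of time, with a further linear segment after the intervention period.

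**The concern.** The intervention starts in whole clinics, and its effect is modelled as a change over time within a clinic. A clinic effect that is constant over time largely cancels from such a contrast. The clinic-level noise that remains is clinic-specific movement around the shared trend, for example a local policy or a change in how one clinic handles refills. The model as described has a place for patient-level serial correlation but names none for this movement.

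The fitted model would then attribute that movement to independent patients and average it down by their number. Two things are at stake. The uncertainty shown around the preliminary effect would be too small. The clinic-by-time variance would also go unestimated, although the Milestones section says the pilot is to support an accurate power calculation for the next trial. If that trial again assigns clinics, this variance is a main planning input.

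**Working it through.** **The plan's own figure.** The article states no standard error, alpha, power or sample-size figure for this model, so there is nothing to reproduce. The check compares the standard error the described model would report with the true one when clinics drift.

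**Inputs from the article.** Eight clinics, four per arm; monthly data; one common linear trend; piecewise effect with knots at the start and midpoint and a later segment; patient-level autocorrelation. Consulting lasts 6 months (Specific Aim 2 paragraph).

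**Assumptions, not in the article.** Total variance 1. Clinic share ICC of 0.01 to 0.05. Of the remainder, 80% is constant within a patient and 20% is AR(1) with monthly correlation 0.5. There are n = 100 patients per clinic, the same ones throughout. There are 12 months before the start, 6 of consulting and 6 after. The clinic effect has correlation r12 over 12 months, so r = r12^(1/12) per month. The provider level is omitted and variances are treated as known.

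**Formulas, on clinic-month means.** J is the all-ones matrix and R(a) has entries a^|lag|.

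- P = [0.8(1 − ICC) J + 0.2(1 − ICC) R(0.5)] / n
- Working covariance (clinic intercept): Vw = ICC·J + P
- True covariance (drifting clinic effect): Vt = ICC·R(r) + P
- B = (X′Vw⁻¹X)⁻¹
- Effect at the end of consulting: L′β = 3b₁ + 3b₂, where b₁ and b₂ are the monthly slopes before and after the midpoint
- Reported SE = √(L′BL)
- True SE = √(L′B X′Vw⁻¹ Vt Vw⁻¹X B L)

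**Results at n = 100, in SD units.** The last column gives the working model a random clinic slope matched to the assumed drift.

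| ICC | r12 | Reported SE | True SE | Ratio | Ratio with clinic slope |
|---|---|---|---|---|---|
| 0.01 | 0.95 | 0.0243 | 0.0291 | 1.20 | 1.05 |
| 0.03 | 0.90 | 0.0241 | 0.0463 | 1.92 | 1.36 |
| 0.05 | 0.80 | 0.0238 | 0.0756 | 3.17 | 2.12 |

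If a 95% interval were formed with ±1.96 reported SEs in the middle case, it would cover 2Φ(1.96/1.92) − 1, about 69%.

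**Dependence on patient numbers (ICC 0.03, r12 0.90, clinic intercept).**

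| n per clinic | Reported SE | True SE | Ratio |
|---|---|---|---|
| 50 | 0.0340 | 0.0521 | 1.53 |
| 100 | 0.0241 | 0.0463 | 1.92 |
| 200 | 0.0170 | 0.0431 | 2.53 |
| 1000 | 0.0076 | 0.0404 | 5.30 |

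Reported SE × √n is constant (0.0340 × √50 = 0.240; 0.0170 × √200 = 0.240), so it falls as 1/√n. The true SE levels off near 0.04, because eight clinics limit it.

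**A second set of assumptions.** Here there are 12 months before, 12 of intervention and 6 after, a clinic ICC of 0.03 and a patient-constant share of 0.60. Clinic AR(1) drift with monthly correlation 0.8 is added at 1% of variance. From 50 to 1000 patients per clinic the reported SE falls from 0.046 to 0.010, while the true SE moves only from 0.083 to 0.070.

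**Length of the intervention period.** The Statistical model section uses a 12-month period and the Specific Aim 2 paragraph a 6-month one. These passages must be reconciled. With 12 months before, 12 of intervention and no later segment, the three intercept-model ratios become 1.28, 2.22 and 3.74, so the point stands under both.

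**The case against.** A reader might infer that the model allows correlation over time only within a patient. The article does not support that: the sentence before the one on autocorrelation covers "Random effects will be included to allow for correlation among repeated observations within the same clinic, provider, or patient". What is confined to the patient is the serial, time-decaying part.

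A reader might also infer that drift is ignored altogether. Drift common to all clinics is in the model, non-linear trends are a planned sensitivity check, and the Limitations section relies on control clinics. Those measures remove common drift only. The provider random effect and provider covariates may absorb part of what happens when a prescriber joins or leaves; the calculation above has no provider level.

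The strongest objection is that the random effects are not said to be intercepts only. A clinic slope is not excluded, and a fuller plan may specify one. This stands, and it makes the larger ratios conditional. It does not close the matter: with a matched clinic slope the ratio is still about 1.0 to 2.2, because a straight line per clinic does not capture month-to-month movement. The article also chose to state at which level serial correlation sits, so this is more than silence.

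Finally, this is a pilot. The article states no test, alpha or interval, and promises point estimates of effect size. The covariance choice does not bias those. To say that the plan will produce false-positive findings would go beyond the text. A patient-level mixed model is also not in itself at odds with a clinic unit of analysis, and the Aim 3 paragraph mentions a matched-pairs comparison. The conflict arises only if clinic-by-time variation is missing from the model.

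**Conclusion.** The concern holds in a conditional form. The article describes clinic, provider and patient random effects, one shared trend and patient-level serial correlation, and names no clinic-specific time term. Read as a clinic intercept, this gives an effect whose standard error follows patient numbers, against the declared clinic unit of analysis.

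Under the stated assumptions the understatement is a factor of 1.2 to 3.2, or about 1.0 to 2.2 if a clinic slope is already intended. These figures are illustrative: ICC, decay, variance shares and patient counts are all assumed, and the size grows with patients per clinic. The direction requires only that clinics drift separately to some degree. The effect estimate itself is not biased; its stated precision is what suffers, along with the planning information for the next trial.

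**What to change.** In the Statistical model section, add a clinic-by-month random effect with decaying correlation, or at the least a random clinic slope, and say which is used.

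Variance terms from eight clinics will be imprecise, so also report a clinic-level check that does not depend on them. Take each clinic's pre-to-post change, form the four within-pair differences, and give their mean with a t interval on 3 df. The half-width is 3.18 × s/√4 = 1.59 s, where s is the standard deviation of the four differences.

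Report the clinic-by-time variance, with its imprecision, as a pilot result for planning the follow-up trial.

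The cost is a change of wording and one or two more variance terms, with no new data. The downside is a wider interval and an extra variance term that will be poorly estimated.
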